##### Administration of surveys/questionnaires to patients

2.9.5.2

Four standardised questionnaires will be administered to the participants. The measures are detailed in sections 2.9.1.2, 2.9.1.3, 2.9.1.4. A conversational approach will be used to elicit information from all participants during the administration of the questionnaires.

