### Study objectives

2.1

The primary objective is to:-compare participants' adherence to haemodialysis regimens (with respect to attendance at scheduled dialysis sessions) between the intervention and control phase.

The secondary objectives are to:-compare participants' adherence to haemodialysis regimens (with respect to adherence to fluid allowances) between the intervention and control phases;-measure change in ratings of quality of life, engagement with self-care and other psychological measures reported by participants between the intervention and control phases;-measure usage and usability of VR by participants;-assess the acceptability and appropriateness of using VR during haemodialysis from the perspectives of patients; and-assess the acceptability and appropriateness of using VR during haemodialysis from the perspectives of clinical staff.

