### Project outcomes

2.9

The primary outcome is attendance at scheduled dialysis sessions.

The secondary outcomes are:-Adherence to fluid allowances between dialysis sessions;-Health related quality of life;-Engagement with self-care;-Depression and anxiety;-Usage, acceptability and usability of VR; and-Participants' (patients and clinicians) satisfaction with VR.

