##### Health-related quality of life and engagement with self-care

2.9.1.2

This will be assessed by the use of the Australian Assessment of Quality of Life (AQoL) scale (6D) [20]. The scale consists of 20 items across 6 dimensions (independent living, relationships, mental health, coping, pain, and senses), and participants are asked which of five descriptive statements best describes their current experience in terms of the item of interest. The scale was chosen for its brevity, validity and conversational style [20]. Reliability of the tool (Cronbach's α) has been found to range between 0.73 and 0.84 [21]. An example of one of the questions in the scale asks the participant to describe their situation over the past week, with respect to “How much energy do you have to do the things you want to do”.

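### Engagement with self-care is listed as an outcome separate from quality of life, but both are assigned to the AQoL-6D with no distinct score; separately, four patient questionnaires are stated and three described

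*Protocol article*

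**What the plan says.** Section 2.1 (Study objectives) includes a secondary objective to "measure change in ratings of quality of life, engagement with self-care and other psychological measures reported by participants", compared between the intervention and control phases. Section 2.9 (Project outcomes) gives "Engagement with self-care" its own entry, next to but separate from health-related quality of life.

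The measurement section, 2.9.1.2, joins the two in its heading, "Health-related quality of life and engagement with self-care", and names one instrument for both, the AQoL-6D. It describes the content as follows: "The scale consists of 20 items across 6 dimensions (independent living, relationships, mental health, coping, pain, and senses". The one sample item it gives is about energy.

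Section 2.9.5 (Data collection processes) schedules the AQoL-6D and the K-5 three times: in the week before the first trial session, in the washout week, and in the week after the trial. The interview based on the User Engagement Scale follows the intervention period.

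Section 2.9.5.2, which concerns patients, states: "Four standardised questionnaires will be administered to the participants". It refers the reader to sections 2.9.1.2, 2.9.1.3 and 2.9.1.4 for the details. The staff survey has its own administration section, 2.9.5.3.

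**The concern.** Two outcomes that are listed separately should be separable in the data. Here one quality-of-life scale serves both, and the article does not say which part of it stands for engagement with self-care. An analyst following the text would have to report the same score twice, or choose a dimension after seeing the data.

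This matters more than its place among the secondary outcomes suggests. Section 2.8 says that this feasibility study puts weight on whether the measures are applicable in this population, and the results are meant to inform a multi-centre trial. The abstract's closing discussion also anticipates that participants may engage more with self-care. A change in AQoL-6D score, read under that label, would be taken as evidence on something the scale, as described, does not visibly measure.

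The questionnaire count is a second and smaller matter. A reader cannot tell from section 2.9.5.2 whether the number is a slip or whether an instrument has gone unnamed.

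**Working it through.** No power or sample-size formula applies. The check is a mapping of outcomes to instruments, followed by a count.

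**Step 1. Secondary outcomes (section 2.9) against their measures (sections 2.9.1.1 to 2.9.1.4).**

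| Secondary outcome | Measure given |
|---|---|
| Adherence to fluid allowances | Weight gain between sessions, from the medical record |
| Health-related quality of life | AQoL-6D |
| Engagement with self-care | AQoL-6D, no separate score named |
| Depression and anxiety | K-5 |
| Usage, acceptability and usability of VR | Headset data, patient interview and staff survey |
| Satisfaction with VR | User Engagement Scale (patients), adapted survey (staff) |

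Of the six, engagement with self-care is the one whose only measure is a scale already assigned whole to another outcome.

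**Step 2. AQoL-6D content as described in section 2.9.1.2.** The six labels are independent living, relationships, mental health, coping, pain and senses. Labels naming engagement with self-care: 0 of 6. Independent living and coping come nearest, but the article maps neither to this outcome.

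**Step 3. Could another listed patient instrument fill the gap?** The K-5 asks about psychological distress. The User Engagement Scale concerns satisfaction with and immersion in the VR experience; its engagement is with the headset content, not with self-care. Neither is assigned to this outcome.

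**Step 4. Count of patient questionnaires in the three sections that 2.9.5.2 cites.**

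- 2.9.1.2: AQoL-6D = 1
- 2.9.1.3: K-5 = 1
- 2.9.1.4: User Engagement Scale, Short Form = 1
- Total for patients: 1 + 1 + 1 = 3, against 4 stated

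The stated figure is reproduced only by adding the staff survey: 3 + 1 = 4. That does not fit. Staff complete it, section 2.9.5.3 handles it separately, and section 2.9.1.4 introduces it by saying that no suitable standardised assessment exists. Leaving out the scale that is built into the interview moves the count further away: 3 − 1 = 2.

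**The case against.** The article does give this outcome an instrument and a schedule. Section 2.9.1.2 names the AQoL-6D for it, and section 2.9.5 collects that scale three times. A reader might therefore infer too much in saying that the outcome has no instrument, no timepoint or no data, or that it cannot be reported at all. The documents do not support that reading. What is missing is anything that separates this outcome from quality of life.

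The scale has 20 items, of which the article quotes one. Independent living or coping might contain items that bear on self-care, and the items are not visible here. This stands, and it limits the criticism to the instrument as the article describes it. Scoring detail is also commonly left to a fuller document. But the article itself makes this a separate outcome and then assigns both outcomes to the whole scale, so the mismatch lies in what it states and not only in what it omits.

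Fluid control between sessions is a form of self-management, and it is measured. The article, however, lists it as its own outcome under adherence to haemodialysis regimens, so it does not supply the self-care measure. The abstract's remark on self-care is conditional and also covers engagement with regimens, which attendance and fluid adherence do measure. Only the self-care half lacks a distinct measure.

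It is tempting to join the two points and infer that the unnamed fourth questionnaire was a self-care scale that fell out of the text. Nothing shows this. A slip that counted the staff survey is at least as plausible, since the cited sections contain four instruments when it is included and section 2.9 uses the word participants for patients and clinicians together. On its own, the count would be an editorial error.

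**Conclusion.** The point holds in two separate parts.

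First, engagement with self-care is listed apart from quality of life, but the only instrument assigned to it is the quality-of-life scale. As described, that scale has no dimension visibly covering the construct (0 of 6), and no distinct score is named. One of six secondary outcomes therefore cannot be reported as distinct from quality of life. This rests on the article's description of the AQoL-6D and would change if a specific dimension or item set were named and justified.

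Second, section 2.9.5.2 states four patient questionnaires and its cited sections describe three. This is an internal contradiction whatever its cause, and no link to self-care is shown.

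The primary outcome, attendance, is unaffected, and so is the sample size, which was not derived from a calculation. The matter is worth correcting because it governs what the study may say about self-care, and the repair is small.

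**What to change.** Choose one of two routes for the outcome and record it in a dated amendment, before baseline assessments if possible, because a baseline or washout measurement that was not taken cannot be recovered later.

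- **Keep the outcome.** In section 2.9.1.2, name a measure of engagement with self-care, or a specific AQoL-6D dimension score with a justification for using it. Collect it at the three timepoints already set for the AQoL-6D.
- **Drop it as a separate outcome.** Remove engagement with self-care from section 2.1, section 2.9 and the heading of section 2.9.1.2. Report the AQoL-6D as quality of life only, and draw no conclusion on self-care engagement from it.

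Independently of that choice, change the count in section 2.9.5.2 from four to three, or name the fourth patient questionnaire and say when it is given.

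The cost is protocol wording. A new measure would add at most one short scale to interviews already planned; an AQoL-6D dimension score would add no data collection.

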##### Administration of surveys/questionnaires to clinical staff

2.9.5.3

Clinical staff will be asked to complete an anonymous questionnaire, adapted from the amended Lindner et al. (2019), satisfaction scale [26] after all dyads have completed the trial. The survey will be accessed via a QR code or a web address.

#### Data management and storage

2.9.6

Patients participating in the study will have a unique study number assigned to them. Data pertaining to conversational interviews with the patient participant group will have identifiers removed following analysis. Data pertaining to attendance, intradialytic weight gain, and psychological measures will be re-identifiable at collection; identifiers will be removed following data cleaning and analysis. Anonymous survey data from the clinicians will be collected electronically through the survey tool hosted on the Qualtrics platform. Partially completed survey responses will be included. The Qualtrics survey data will be hosted on the James Cook University server. Other study documents will be stored at TUH.

All data obtained will remain confidential and will be securely stored throughout the course of the study within locked cupboards/filing cabinets, to which only the research team members have access. Computer files will be accessible only to the research team. Participants in the trial will not be identifiable in any reports, publications or presentations arising from the study. This study has ethics approval from the Health service's Human Research and Ethics Committee (HREC/QTHS/72273).

#### Data analysis plan

2.9.7

The quantitative data will be entered into an IBM SPSS software (SPSS) database (Version 25, Chicago). Chi-square tests will be used to analyse categorical data. Ordinal data will be analysed via rank tests. Paired t-tests and ANOVA will be used for continuous variables where appropriate. Where assumptions of normality have been violated, non-parametric versions of tests will be used. If participants withdraw, attendance data will be analysed by intention-to-treat. Where appropriate, modelling of outcomes will be undertaken in order to explain variability in results.

Qualitative analysis will include notes taken from informal interviews with patients and will be analysed deductively. Observational and summary notes taken by the investigators, and notes taken by a Stakeholder Group (comprising patient, staff and researcher representatives, who will meet to discuss the progress of the study at least monthly) will also form part of the analysis.

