#### Project outcome measures

2.9.1

Note that the crossover design means that differences being examined are *within* participants [16]. That is, outcomes in the intervention phase are compared to outcomes in the control phase for all participants.

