##### Adherence to haemodialysis regimens will be measured by

2.9.1.1

-difference in participants' attendance rates when in the intervention phase compared to the control (non-intervention) phase; and-difference in proportions of participants' adherence to fluid allowances, defined as gaining, on average, no more than 1 kg per day between dialysis sessions in the intervention phase compared to the control phase [2].

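### Chi-square tests are named for categorical data with no paired form, although fluid adherence compares the same 40 people in two phases

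*Protocol article*

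**What the plan says.** Section 2.2 describes a crossover in which each participant serves as his or her own control, and gives the smaller number of participants needed as one reason for it. Section 2.9.1 repeats the within-person principle: "outcomes in the intervention phase are compared to outcomes in the control phase for all participants".

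Section 2.9.1.1 gives the fluid measure as the "difference in proportions of participants' adherence to fluid allowances, defined as gaining, on average, no more than 1 kg per day between dialysis sessions", compared between the two phases.

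Section 2.9.7 then assigns tests by type of data. For categorical data: "Chi-square tests will be used to analyse categorical data". For continuous data: "Paired t-tests and ANOVA will be used for continuous variables where appropriate". Two further clauses might bear on the point: "Where assumptions of normality have been violated, non-parametric versions of tests will be used", and "Where appropriate, modelling of outcomes will be undertaken in order to explain variability in results".

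The sample is 8 clusters of 5 patients. Section 2.8 says that this number does not come from a statistical calculation.

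**The concern.** A threshold applied to a participant's average gain over a phase yields one yes or no for that phase. Each participant supplies two such answers, so the comparison is of paired binary data. The ordinary chi-square test compares proportions in two separate groups and takes all 80 answers as independent. The plan names pairing for t-tests but for no categorical method, so an analyst who follows the text would run the unpaired test.

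At stake are the standard error and p-value for the first secondary outcome. If people who keep to their allowance in one phase tend to do so in the other, which is the premise of the crossover, the unpaired test discards that information. It also never shows how many people changed status between phases, which is the count needed to plan a later paired comparison. Section 3 says that the results will inform a multi-centre trial.

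**Working it through.** **Plan's own figure.** There is no power calculation to reproduce. The sample agrees arithmetically: 8 × 5 = 40.

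**Do other clauses supply a paired test?** The non-parametric clause is triggered by non-normality, a property that a yes/no outcome does not have. The modelling clause is optional, serves to explain variability, and names no within-person model. Neither replaces the chi-square for this outcome.

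**Inputs.** n = 40 pairs, from the protocol. Assumed, because the document gives none: adherence of 50% on control and 70% on VR, two-sided alpha 0.05, and within-person correlation phi of 0, 0.3 and 0.5. Clustering and period effects are left out.

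**Standard error of the difference.**

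- Unpaired: √[(p₁q₁ + p₂q₂)/n] = √[(0.25 + 0.21)/40] = 10.7 points, whatever phi is.
- Paired: √[(p₁q₁ + p₂q₂ − 2·phi·√(p₁q₁p₂q₂))/n].
  - phi 0: 10.7 points.
  - phi 0.3: √[(0.46 − 0.6 × 0.2291)/40] = 9.0 points.
  - phi 0.5: √[(0.46 − 0.2291)/40] = 7.6 points.

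At phi 0.5 the variance ratio is 0.46/0.2309 = 2.0, so the unpaired formula uses about half the information.

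**Power and type I error.** For each phi, the probability of being adherent in both phases is p₁p₂ + phi·√(p₁q₁p₂q₂), and the other three cells follow by subtraction. Every possible table of 40 pairs was enumerated and the tests applied: Pearson chi-square on two groups of 40 without continuity correction, asymptotic McNemar (b − c)²/(b + c), and exact McNemar. Here b and c are the two discordant counts.

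| phi | Chi-square power | McNemar power, asymptotic | McNemar power, exact | Chi-square type I error (50% v 50%) |
|---|---|---|---|---|
| 0 | 46% | 45% | 35% | 5.7% |
| 0.2 | 45% | 52% | 43% | 3.3% |
| 0.3 | 45% | 57% | 48% | 2.3% |
| 0.5 | 43% | 73% | 63% | 0.7% |

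Under no effect, asymptotic McNemar rejects in 4.3% to 5.3% of trials over the same range, and exact McNemar in 2.2% to 3.0%.

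**Worked example.** Suppose that 28/40 are adherent on VR and 20/40 on control: 18 in both phases, 10 on VR only, 2 on control only, 10 in neither (phi 0.44).

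- Chi-square: pooled proportion 48/80 = 0.6, and 0.20²/(0.6 × 0.4 × 2/40) = 3.33, p = 0.068.
- McNemar: (10 − 2)²/12 = 5.33, p = 0.021; exact p = 0.039.
- Standard error: unpaired 10.7 points (95% interval ±21); paired √(12 − 8²/40)/40 = 8.1 points (±16).

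The same data fall on opposite sides of 5%.

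**The case against.** The sentence in 2.9.7 is one general line in a condensed article. It does not mention fluid adherence, McNemar's test is itself a form of chi-square, and the trial has truly unpaired categorical data in the clinician survey and the baseline characteristics. A fuller analysis plan may name the paired form. This stands as a reason to ask for clarification rather than to assume a settled error. It does not remove the point, because the text names pairing where it applies to means and not where it applies to proportions.

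The outcome type is not beyond doubt either. If adherence were scored as each participant's share of intervals within allowance, it would be continuous and the paired t-test would apply. The threshold on an average makes the yes/no reading likelier.

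The gain is not guaranteed. At phi 0 there is nothing to recover, and exact McNemar has less power than the chi-square until phi is close to 0.25. Nor do the documents show that the trial could detect any particular effect, since they state neither an effect size nor power.

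Two stronger inferences are tempting and should not be drawn. The first is that the test would produce false claims of benefit; with positive correlation it does the reverse. The second is that a chi-square on individual sessions (40 × 12 = 480 scheduled per phase) must understate the standard error. The direction depends on how much the phase effect varies between people. In simulations with an assumed person standard deviation of 1.5 on the logit scale and no effect, type I error was about 2% with no such variation and exceeded 5% only when that variation was large. Session-level scoring would also depart from the average-based definition in 2.9.1.1.

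**Conclusion.** The point holds in limited form. Taken literally, 2.9.7 gives a paired yes/no outcome a test that assumes independent groups. For an assumed 50% against 70%, the loss against asymptotic McNemar runs from nothing at phi 0 to about 12 percentage points of power at phi 0.3 and 29 at phi 0.5, while the chi-square's true type I error falls well below the nominal level. Against exact McNemar the difference is about −10, +3 and +19 points.

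All of this rests on assumed adherence rates and correlation, on the yes/no reading of the outcome, and on leaving clusters and periods aside.

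Severity is moderate. The outcome is secondary, section 2.8 puts less weight on hypothesis testing, the error is conservative, and the data can be re-analysed. A reader might infer that the primary outcome is also affected. The documents do not support that: attendance is compared as a rate per participant, for which 2.9.7 offers paired tests.

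**What to change.** In 2.9.7, state that yes/no outcomes compared between phases are analysed by a paired method. Either of these would do:

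- McNemar's test, saying whether asymptotic or exact, with a paired confidence interval for the difference in proportions and the two discordant counts reported.
- A conditional or mixed-effects logistic model with terms for phase and period.

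Restrict chi-square to comparisons between different people, such as baseline description or the clinician survey. In 2.9.1.1, say outright that fluid adherence is scored once per participant per phase, if that is what is meant.

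The cost is a sentence or two of wording, with no added patients, visits or data.

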### Project design

2.2

A crossover RCT will be conducted where participants are their own control. Such a study design requires fewer participants, maximises equivalence between groups and controls for confounding variables [16], compared to traditional parallel RCTs. Consistent with this design, a one-week washout period between the intervention and control phases will be included to minimise any carry over effects [16]. Clusters have been determined by place of dialysis (in-centre or satellite dialysis unit), and scheduled days of dialysis. Each of the 8 clusters will consist of 5 participants (as described later in section 2.9.4).

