### Sample size calculation

2.8

The sample size of Group 1 (patients) of n = 40 is informed by other feasibility studies included in our recent systematic review [6]. The within-subject crossover design minimises sample variability as all participants act as their own controls [19]. Given that the current study is a feasibility analysis, there is less emphasis on hypothesis testing and more upon the appropriateness of the intervention and applicability of the measures for assessing physical and psychological status in this patient population. Our sample size for this feasibility study is based upon empirical literature reports of similar studies and practical limitations upon recruitment, rather than statistical calculations.

With regards to the clinicians (Group 2), we will invite all clinicians (nurses, medical officers, allied health staff) to complete an anonymous questionnaire. It is anticipated that approximately 50% of clinicians will participate.

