#### Randomization

2.9.4

There will be 8 clusters of patients to be randomised (4 × 2 dyads) organised by location of dialysis (TUH or NW), day of the week (Monday-Wednesday-Friday roster or Tuesday-Thursday-Saturday roster) and time of dialysis (morning or afternoon). Randomization will be to VR (intervention) or usual activities (control) (Fig. 1).

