**Fig. 1 fig1:**
[figure not shown]
Design of Cross-over Randomised Controlled feasibility study.

To avoid contamination, clusters will be randomised (using web-based computer program, for example www.randomization.com) [27] within dyads as to which cluster receives VR first. Whilst it is not possible to ‘blind’ participants and unit staff to the allocation, the investigators analysing the data will be blinded to group assignment.

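### Section 2.9.7 names participant-level tests that ignore period, although the order of VR and control is randomised to 8 rosters within 4 dyads, so intervals may be too narrow or too wide

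*Protocol article*

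**What the plan says.** **Design.** Section 2.2 of the protocol article fixes the cluster size: "Each of the 8 clusters will consist of 5 participants". Section 2.9.4 states "There will be 8 clusters of patients to be randomised (4 × 2 dyads", with clusters formed by dialysis unit, weekday roster and time of day. A web-based program then decides "within dyads as to which cluster receives VR first". The order of the two phases is thus assigned to a whole roster, not to a patient.

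**Primary contrast.** Section 2.9.1.1 compares each participant's attendance rate in the VR phase with the same person's rate in the control phase.

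**Analysis.** Section 2.9.7 lists methods by type of data: chi-square tests for categorical data, rank tests for ordinal data, and then "Paired t-tests and ANOVA will be used for continuous variables where appropriate". It adds a fallback: "Where assumptions of normality have been violated, non-parametric versions of tests will be used". One further sentence allows modelling, where appropriate, with the purpose of explaining why results vary. The section mentions neither cluster, dyad, period nor order, and it does not say which test applies to attendance.

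**Sample size.** Section 2.8 bases n = 40 on the literature and on "practical limitations upon recruitment, rather than statistical calculations".

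**The concern.** The five patients of a roster share shift, staff and calendar weeks in each phase. If something changes for that roster in one phase (staffing, transport, a local event), or if VR works better in some rosters than in others, their VR-minus-control differences are correlated. A test that counts 40 independent differences then overstates the information.

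A second fault acts the other way. A general shift between the first and second phase enters the differences with opposite signs in the two orders. With equal cluster sizes it cancels from the estimate, but it inflates the standard deviation on which a paired test relies, so the interval becomes too wide.

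Attendance is both the primary objective (section 2.1) and the primary outcome (section 2.9), and the results are meant to inform a multi-centre trial. What is at stake is whether the interval around the attendance difference can be trusted when that trial is planned.

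**Working it through.** **1. The plan's own figure.** 2 units × 2 weekday rosters × 2 times of day = 8 clusters, and 8 × 5 = 40, which agrees with section 2.8. The article states no alpha, SD, intracluster correlation or power, so there is nothing further to reproduce.

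**2. Model for the differences.** For participant i in cluster j, write the VR-minus-control difference as d = τ + s·π + c + e. Here τ is the VR effect, s is +1 or −1 according to order, π is the period shift, c is a cluster term and e an individual term. Stable person and roster effects have already gone through pairing. Let c + e have variance 1, with a share ρ due to c.

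- Standard error from a paired t-test: s.d.(d)/√40, on 39 df.
- True variance of the mean: [1 + (5 − 1)ρ]/40. The period term drops out, because four clusters of 5 carry +π and four carry −π.
- Ratio of true to naive standard error with π = 0: approximately √(1 + 4ρ).
- With ρ = 0 and π = 0.5 SD, the observed variance is about 1 + 0.25 = 1.25, so the naive standard error is about √1.25 = 1.12 times too large.

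**3. Type I error at an assumed two-sided 5%.** Normal differences, no VR effect, 40,000 simulated trials per setting (simulation error about √(0.05 × 0.95/40,000) = 0.1 percentage points). The values of ρ and π are assumptions. Dyad means are tested on 3 df.

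| ρ | 1 + 4ρ | SE ratio | Effective N = 40/(1 + 4ρ) | Paired t, no shift | Paired t, 0.5 SD shift | Dyad means, no shift | Dyad means, 0.5 SD shift |
|---|---|---|---|---|---|---|---|
| 0 | 1.00 | 1.00 | 40.0 | 4.9% | 2.9% | 5.0% | 4.7% |
| 0.01 | 1.04 | 1.02 | 38.5 | 5.5% | 3.1% | 5.0% | 4.9% |
| 0.02 | 1.08 | 1.04 | 37.0 | 6.0% | 3.4% | 5.0% | 4.9% |
| 0.05 | 1.20 | 1.10 | 33.3 | 7.4% | 4.4% | 5.0% | 4.9% |
| 0.10 | 1.40 | 1.18 | 28.6 | 9.6% | 6.5% | 5.2% | 5.0% |
| 0.20 | 1.80 | 1.34 | 22.2 | 14.6% | 10.6% | 5.0% | 5.0% |

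Repeat simulations gave 14.2% to 14.6% in the last row for the paired t-test without a shift. The paired t-test is valid when ρ and π are both zero, and the two faults nearly offset each other at ρ = 0.05 with a 0.5 SD shift. Dyad means hold about 5% in every row.

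**4. Which cluster-level analysis.** An alternative compares the 4 VR-first clusters with the 4 control-first clusters on 6 df. It removes a period shift common to all, but not one that differs between dyads. Sections 2.6 and 2.9.5.3 suggest that dyads may run at different times. With dyad-specific shifts of SD 0.5 (assumed), the 6-df test rejects only 1.3% to 1.7% of the time, while the dyad-paired test stays at about 5%.

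**5. Price of the dyad analysis.** t(0.975) is 2.023 on 39 df and 3.182 on 3 df, a ratio of 1.57. Multiplied by the SE ratio, the interval is 1.57 times the naive width at ρ = 0 and 1.34 × 1.57 = 2.11 times at ρ = 0.20. Four dyads give 2⁴ = 16 allocations, so the smallest two-sided randomisation p-value is 2/16 = 0.125 whichever analysis is chosen.

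**The case against.** A reader might infer that the error bars for attendance are simply wrong, and too small. The documents do not support that. Pairing already removes the largest sources of correlation, the article gives no figure for what remains, and the table shows errors in both directions as well as settings with almost none. With equal cluster sizes, the fault affects precision and does not bias the estimate.

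A reader might also take it as stated that attendance will be tested by a paired t-test on 39 df. Section 2.9.7 is a list by data type, qualified by appropriateness, and names no test for attendance. The paired t-test is an inference from the outcome being a within-person rate. The inference matters little, because the rank and chi-square alternatives as ordinarily applied also treat participants as independent. That the non-parametric fallback makes things worse has not been shown, since no rank test was simulated.

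Two general defences remain. The first is that an article condenses, and model terms are commonly left to a fuller document. That would excuse silence, but this section positively names tests that do not match its own randomisation, and the optional modelling has a different purpose. The second is that section 2.8 plays down hypothesis testing and the study is about feasibility, with no alpha or decision rule. This stands and lowers the weight of the point. It does not remove it, because an interval of unknown accuracy for the primary outcome is still a poor basis for the next trial.

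**Conclusion.** The point holds as a mismatch between a stated method and the design: the named tests take no account of randomisation by cluster within dyads, or of period. Under an assumed correlation of 0.02 to 0.20 and no period shift, a nominal 5% paired t-test has a true error of about 6% to between 14% and 15%. Under an assumed 0.5 SD shift and no correlation, it has about 3%. These figures also assume normal differences, five patients in every cluster and a two-sided 5% level. The actual size and direction cannot be known from the article. It should be fixed, but since no stated decision depends on a significance test, it is not a defect that must be resolved before the trial can go ahead.

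**What to change.** In section 2.9.7, replace the participant-level phase comparisons with an analysis by randomised unit:

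- Compute each participant's VR-minus-control difference and average within each cluster.
- Average the two cluster means of each dyad. The two clusters have opposite orders, so the dyad's period shift cancels, provided that both run over the same weeks.
- Report the mean of the 4 dyad values with a 95% t interval on 3 df.

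An alternative is a mixed model with fixed phase, period and dyad-by-period, random cluster, cluster-by-period and participant, and small-sample degrees of freedom. The 16 cluster-period means less 8 dyad-by-period cells, 4 cluster contrasts within dyads and 1 phase effect again leave 3 df.

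With either method, present the estimate and its interval rather than a significance verdict, since four dyads cannot support a firm test.

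**Cost.** Wording only, with no new data. The interval is wider (multiplier 3.18 against 2.02), which reflects the true precision of 4 dyads.
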